## Abstract

**Background:**

Online social networking and personally controlled health management systems (PCHMS) offer a new opportunity for developing innovative interventions to prevent diseases of public health concern (e.g., influenza) but there are few comparative studies about patterns of use and impact of these systems.

**Methods/Design:**

A 2010 CONSORT-compliant randomised controlled trial with a two-group parallel design will assess the efficacy of a web-based PCHMS called *Healthy.me *in facilitating the uptake of influenza vaccine amongst university students and staff. Eligible participants are randomised either to obtain access to *Healthy.me *or a 6-month waitlist. Participants complete pre-study, post-study and monthly surveys about their health and utilisation of health services. A post-study clinical audit will be conducted to validate self-reports about influenza vaccination and visits to the university health service due to influenza-like illness (ILI) amongst a subset of participants. 600 participants older than 18 years with monthly access to the Internet and email will be recruited. Participants who (i) discontinue the online registration process; (ii) report obtaining an influenza vaccination in 2010 before the commencement of the study; or (iii) report being influenced by other participants to undertake influenza vaccination will be excluded from analysis. The primary outcome measure is the number of participants obtaining influenza vaccination during the study. Secondary outcome measures include: number of participants (i) experiencing ILI symptoms, (ii) absent from or experiencing impairment in work or study due to ILI symptoms, (iii) using health services or medications due to ILI symptoms; (iv) expressing positive or negative attitudes or experiences towards influenza vaccination, via their reasons of receiving (or not receiving) influenza vaccine; and (v) their patterns of usage of *Healthy.me *(e.g., frequency and timing of hits, duration of access, uptake of specific functions).

**Discussion:**

This study will provide new insights about the utility of online social networking and PCHMS for public health and health promotion. It will help to assess whether a web-based PCHMS, with connectivity to a health service provider, containing information and self-management tools, can improve the uptake of preventive health services amongst university students and staff.

**Trial registration:**

ACTRN12610000386033 (Australian New Zealand Clinical Trials Registry)

## Background

Influenza is an important contributor to population morbidity and mortality. Despite the unpredictable nature of influenza severity and spread on a population scale, understanding the behaviour of individual patients during seasons of respiratory disease has become essential for the planning and execution of successful public health interventions. However, current knowledge is based largely on observational studies, and randomised controlled experiments that test different public health interventions are urgently needed [1].

The pandemic of Influenza A H1N1 (Swine Flu) in 2009 and 2010 provided a major challenge to health services around the world. Similar to previous pandemics, it has led to significant aberrations in consumer behaviour, such as the stockpiling of goods, the victimisation of specific population groups, the cancellation of travel and the boycotting of particular foods (e.g., pork). Furthermore, large regional differences in risk estimation and risk perception have potentially affected the uptake of vaccination and other public health measures [2]. The pandemic prompted search for novel and innovative containment interventions as many traditional public health measures failed to control the spread of influenza infection. In particular, increasing the uptake of vaccination and ensuring compliance with containment policies have become a major challenge for public health and health authorities. The clinical picture in severe cases of pandemic (H1N1) 2009 influenza was also markedly different from the disease pattern seen during epidemics of seasonal influenza, in that many of those affected were previously healthy young adults with complex social interaction patterns. This group represents users of healthcare services who are most likely to be receptive to personal health records (PHRs), offering an opportunity to study and potentially modify healthcare information seeking and service utilization behaviour in young adults.

Online social networking and personally controlled health management systems (PCHMS) offer a new opportunity for developing innovative interventions to prevent diseases of public health concern [3]. Health promotion programs based on PCHMS can be used in a variety of settings targeting a large range of health issues, including the prevention of influenza [1]. Consumers are increasingly using such online systems to inform health decisions and manage their health. The uptake of PCHMS is likely to vary in different social groups under different conditions and within different contexts [4], but few comparative studies are available about patterns of use and impact of these systems.

It is thus important to ensure that design of studies to test the impact of online PCHMS adequately reflects the increased complexity of such interventions. This randomised controlled trial (RCT) will make a specific and significant contribution to our understanding on the efficacy of using a web-based PCHMS called *Healthy.me*, developed at the University of New South Wales, in improving the uptake of influenza vaccination in a university setting.

### Study aims and hypotheses

Specific hypotheses to be tested in this study are that:

1. Consumers using a PCHMS are more likely to comply with public health recommendations, as measured by their rates of seeking and obtaining influenza vaccination;

2. PCHMS that provides online facilities to schedule encounters with a health service provider will increase the utilisation rate of those services.

## Methods/Design

### Study design

A randomised controlled trial with a two-group parallel design (with intervention allocation ratio 1:1) is used to evaluate the efficacy of *Healthy.me*, reported in accordance to the 2010 CONSORT statements (Figure 1) [5]:

**Figure 1 F1:**
[figure not shown]
**Overview of RCT process**.

• Participants randomised to the *intervention *group will have immediate access to *Healthy.me *from the date they are recruited in addition to health care of usual standard.

• Participants randomised to the *control *group will receive usual care. They will be allocated to a waiting list and delayed to use *Healthy.me *by approximately six months.

### Participants and setting

Table 1 outlines participant inclusion and exclusion criteria. The study will recruit students and staff members at UNSW who are fluent in English. Written material advertising the study outlines participant inclusion criteria, which are self-explanatory (i.e. age ≥ 18 and monthly access to Internet and email). Exclusion criteria are applied post-study. Hence, participants who self-identify as meeting inclusion criteria proceed to first providing informed consent before commencing the pre-study survey.

**Table 1 T1:** Eligibility criteria for participants

Inclusion criteria	Exclusion criteria
1. Aged 18 or above.	1. Participants who did not complete registration process [excluded before randomization].

1. Access to the Internet, and email at least on a monthly basis.	2. Participants who self-reported having obtained an influenza vaccination in 2010 prior to enrolment in the study [excluded from analysis].

	3. Participants who self-reported to be influenced by other participants during the study to obtain (or not obtain) influenza vaccination [excluded from analysis].

Participants engage in this trial online in their own space at their own time. All participants are required to complete online (i) a 5-10 minute pre-study survey; (ii) a monthly one-minute survey to collect their health symptoms and health service use; and (iii) a 5-10 minute post-study survey. Participants allocated to the *Healthy.me *group are also required to complete a five-minute mandatory online tutorial about system before commencing the study. Those who complete all study surveys will enter into a draw for $500 prize at study completion.

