**Figure 2 F2:**
[figure not shown]
**Features of *Healthy.me *(^© ^University of New South Wales, 2009-2012)**.

1. Personal Record: Allows for self-recording of medical test results and health measurements (not available to participants in this study).

2. Pillbox: Allows for self-recording of current medications and medication adherence.

3. Schedule, to-do list and reminders: An online schedule to self-record and keep track of health-related appointments, to-do items, which sends email reminders.

4. Team: A feature that allows the self-recording of clinical and non-clinical personnel looking after one's health.

5. Journeys: Consumer-specific care pathways that provide knowledge in an actionable way. A feature that describes the different stages in the management of health conditions that can be used to personalise other PHR sections in the system, and provides advice on what to expect and how to prepare for each stage. (Participants in this study had access to an influenza vaccine journey).

6. Social features for this study included: (i) a profile for each member to store and customise their personal information, (ii) the ability to send and receive messages with other members on *Healthy.me*.

Studies suggest that by addressing both knowledge-based (e.g. lack of awareness) and system-based (e.g. inconvenience) barriers in accessing health services, patients and consumers are more likely to uptake preventative health measures, such as influenza vaccination [6]. Our PCHMS is designed to address both knowledge-based and system-based barriers faced by consumers when accessing and utilising health services.

The PCHMS thus integrates a number of tools to address knowledge and system barriers that influence consumers' engagement with health services. Our PCHMS contains a PHR, as well as online social networking mechanisms that allow participants to interact with healthcare professionals at the service provider and other consumers, and additional tools to support consumer decision making and subsequent task management. In addition, it is integrated with consumer-specific care pathways (called "journeys") that provide knowledge in an actionable way. For example, at the point that a consumer encounters advice to seek influenza vaccination, they are immediately able to book an appointment with a medical practitioner, or set themselves a reminder.

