### Sample size considerations

The sampling unit is the participant and the unit of analysis is also the participant. A conservative estimate of 600 participants with 300 in each group is needed to detect a 10% difference in influenza vaccination rate between the control group (15%) and the intervention group (25%). This estimate is calculated at 5% level of significance, 80% power (two-sided test), with an anticipated participant dropout rate around 10% [12].

The effect size estimate is based on a review assessing the effectiveness of patient reminder systems in improving immunization rates, which can range from 5 to 20% [13]. The baseline rate estimate of influenza vaccination was informed by our audit conducted at the University Health Service, showing 16% of patients at the practice received FluVax or PanVax between 5/3/2009 to 5/11/2009. This estimate is also supported by literature reporting 18 to 30% of university students and healthy adults (18 to 49 years old) obtaining influenza vaccination in a year [14,15].

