#### Blinding and assessment

Since *Healthy.me *is a behavioural intervention it is not possible to completely blind participants to the intervention. The group allocation is revealed to participants only after obtaining their consent to participate in the study and completion of the pre-study survey. However, investigators and clinicians involved in the study are blinded to group allocation. To minimise contamination of control participants who might interact with participants who are part of the intervention group, participants in the intervention group are asked not to share their *Healthy.me *access details with other people. Further, participants who self-reported to have been influenced by others participating in the study to obtain (or not obtain) influenza vaccination will be excluded from analysis. To assess the success of blinding, administrative staff at the University Health Service will be consulted at study completion to confirm whether clinicians involved in assessing patient outcomes and/or administrating influenza vaccination are able to distinguish patients who booked an appointment using *Healthy.me*.

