• *Social influence and access to Healthy.me*: The social networks of individual participants may span the intervention and control arms of this study, and see intervention subjects un-blind control subjects with information obtained from the intervention. As this is a pragmatic trial in the real world, such effects cannot be controlled for. Indeed participants' social networks are likely to influence access to Healthy.me if the intervention was in routine use. We will attempt to measure this effect by asking participants in the control arm if they have been in contact with intervention arm subjects. If a significant group is identified, we will conduct separate analyses to estimate the impact of any such effect on overall trial results.

• *Baseline comparisons*: As this is a pragmatic trial of a multifaceted intervention in a complex environment, it is possible that baseline variables associated with subjects might also influence the outcome. For example, having a prior history of obtaining influenza vaccination may predict future vaccination rates, independently of any additional intervention. We will identify potential baseline variables that might influence outcome, including gender, and test for unequal distribution of these variables in the intervention and control populations. Should there be a significant difference in their distribution due to chance bias, these will be fitted in an analysis of covariance to model their impact on any observed differences between the two arms [39].

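### Exclusion criterion 3 removes participants from the primary analysis after randomisation, on their own unblinded account of why they did or did not have the primary outcome

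*Protocol article*

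**What the plan says.** Table 1 (Participants and setting) gives the third exclusion criterion as "Participants who self-reported to be influenced by other participants during the study to obtain (or not obtain) influenza vaccination [excluded from analysis". The text above the table says that exclusion criteria are applied once the study is over. Outcome measures then states that anyone meeting them is left out of the primary-outcome analysis. Blinding and assessment repeats the rule as a step against contamination: those "influenced by others participating in the study to obtain (or not obtain) influenza vaccination will be excluded from analysis". Neither place limits it to one arm.

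Three other places bear on the point:

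- Description of intervention, item 6, lists among the social features of the system "the ability to send and receive messages with other members". Controls have no access to the system for about six months.
- Outcome measures and Primary analysis both keep intervention participants who never used the system.
- The Limitations item on social influence says "As this is a pragmatic trial in the real world, such effects cannot be controlled for", notes that social networks would also act in routine use, and plans to ask controls about contact with intervention participants, with separate analyses if a sizeable group is found.

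**The concern.** A randomised comparison is protected because who is analysed does not depend on what happened after allocation. Criterion 3 makes it depend on exactly that. The participant knows the allocation, is asked at the end why he or she was or was not vaccinated, and is removed according to the answer. Criterion 2, vaccination before enrolment, differs in kind because allocation cannot have caused it.

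The arms are also unlikely to be affected alike. Only the intervention arm can exchange messages inside the system. A member persuaded that way is a success of the intervention, and the rule deletes that success. A control persuaded by an intervention participant is contamination, and the rule deletes that too. The first deletion lowers the estimated effect and the second raises it. The analysed set alone cannot show which dominates. At stake is whether the primary result answers the trial's question: does giving people the system raise vaccination?

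**Working it through.** **Inputs from the protocol (Sample size considerations).** Control 15%, intervention 25%: "detect a 10% difference in influenza vaccination rate between the control group (15%) and the intervention group (25". Two-sided 5% level, 80% power, about 10% dropout: "This estimate is calculated at 5% level of significance, 80% power (two-sided test), with an anticipated participant dropout rate around 10". Stated size: "A conservative estimate of 600 participants with 300 in each group is needed".

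**The plan's own figure.** Uncorrected two-proportion formula, mean rate 0.20:

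n = [1.96·√(2·0.20·0.80) + 0.8416·√(0.15·0.85 + 0.25·0.75)]² / 0.10² = 1.581² / 0.01 ≈ 250 per arm.

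With continuity correction: (250/4)·[1 + √(1 + 4/(250·0.10))]² = 62.5·2.077² ≈ 270 per arm. Allowing for dropout: 270/0.90 = 300 per arm, 600 in total. The stated size reproduces and is not in question. With 270 evaluable per arm, the power of the uncorrected χ² test is 83%.

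**Effect of criterion 3.** The document gives no rate for it, so every rate below is an assumption. Let p be the true vaccination rate in an arm, a the share of the arm reporting influence to vaccinate (all vaccinated), and b the share reporting influence not to (all unvaccinated). Then

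analysed rate = (p − a)/(1 − a − b), analysed n = 270·(1 − a − b).

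Power uses the two-proportion test (pooled variance under the null) on the reduced numbers. In every row except the first, b = 1% in both arms.

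| a, control / intervention | Control rate | Intervention rate | Difference | Power |
|---|---|---|---|---|
| rule not applied | 15.0% | 25.0% | 10.0 points | 83% |
| 1% / 4% | 0.14/0.98 = 14.3% | 0.21/0.95 = 22.1% | 7.8 points | 64% |
| 1% / 2% | 0.14/0.98 = 14.3% | 0.23/0.97 = 23.7% | 9.4 points | 79% |
| 1% / 1% | 0.14/0.98 = 14.3% | 0.24/0.98 = 24.5% | 10.2 points | 85% |
| 3% / 1% | 0.12/0.96 = 12.5% | 0.24/0.98 = 24.5% | 12.0 points | 94% |

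**Each mechanism alone (b = 0).**

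- If 2 of the intervention arm's 25 points come through peers and are removed, the difference is 0.23/0.98 − 0.15 = 8.5 points instead of 10.0.
- If spillover lifts controls from 15% to 17% and those 2 points are removed, the difference is 0.25 − 0.15/0.98 = 9.7 points, against 8.0 in the arms as randomised.

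**No difference between arms.** With 15% in both arms and equal exclusion, the rejection rate stays at 5%. With the 1% / 4% pattern the analysed rates are 14.3% and 0.11/0.95 = 11.6%, a spurious −2.7 points, and the two-sided rejection rate is about 15%. This case requires the extra peer-driven vaccinations in the intervention arm to be offset exactly elsewhere, so it shows the mechanism and is not a forecast.

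**The case against.** The rule is deliberate, disclosed and has a purpose. Blinding and assessment offers it as protection against contamination, in a trial that sets out to assess efficacy. If only controls are affected, it brings the estimate closer to the contrast without contamination: in the spillover case above, 9.7 points against an uncontaminated 10.0, where the arms as randomised give 8.0. By the same reasoning, the 12.0-point row is inflated only relative to the as-randomised contrast. If those 3% of controls were vaccinated solely through contamination, the uncontaminated control rate would be 12% and the contrast 13 points. The harm also depends on numbers nobody has: with small and equal exclusions, little changes.

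All of that stands as a limit on size. It does not rescue the rule, which also applies to the intervention arm, where peer contact is part of what is being tested, and which selects on the reason for the outcome in both arms.

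Four stronger readings are tempting but not supported:

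- *That Limitations says the opposite.* It concerns contact reported by controls, whereas criterion 3 concerns influence reported by anyone. A plan can do both. Calling the effects uncontrollable while excluding for them is a tension, not a reversal.
- *That the Abstract sets a different rule.* Its wording, "report being influenced by other participants to undertake influenza vaccination will be excluded from analysis", covers one direction only, but Table 1 and Blinding and assessment agree on both directions. The Abstract reads as an abbreviation.
- *That the comparison is certainly lost, or biased in a known direction.* Neither follows without exclusion rates by arm.
- *That every randomised participant must be restored.* Criterion 2 and unknown vaccination status are separate matters, and this point makes no case about them.

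**Conclusion.** The point holds. Criterion 3 is an outcome-related exclusion after randomisation, applied to the primary analysis on unblinded self-report, and no section withdraws it. Retaining non-users does not offset it, and the conditional contact analysis in Limitations neither restores the excluded participants nor shows what their exclusion did.

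Its direction and size cannot be determined from the document. Under the assumed rates the analysed difference lies between 7.8 and 12.0 points around a true 10.0, with 10.2 points in the symmetric case. The low end rests on an assumed fourfold imbalance in peer-driven vaccination, and the high end on a threefold imbalance the other way. The correction matters even if few are excluded, because the rule defines the primary comparison and the sign of any bias could not be recovered afterwards.

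**What to change.** Remove criterion 3 as a condition of the primary analysis set in Table 1, in Blinding and assessment and in the Abstract. State that participants otherwise eligible for the primary analysis are analysed in their randomised arm regardless of reported peer influence. Leave criterion 2 and the handling of unknown vaccination status as they are for this purpose.

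Keep the influence question in both arms and tabulate the answers by arm and by direction. Use exclusion on influence only as an added sensitivity analysis. It would stand beside the control-arm contact analysis in Limitations, which covers a different variable and one arm only.

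The cost is protocol wording and one extra analysis, with no additional participants: 270 evaluable per arm still gives 83% power for 15% against 25%. The downside is that contamination of controls stays in the primary estimate and may dilute it slightly.

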#### Recruitment strategy

Five methods will be used to invite students and staff at UNSW to participate in the study (to avoid influencing consumer behaviour, it is not explicit to infer from advertising material that the study is about influenza or influenza vaccination):

1. Weekly and monthly advertisements circulated in online and print newsletters and magazines to staff and students.

2. Online announcements circulated for students and staff on UNSW home page, myUNSW home page, UNSW elearning portals and UNSW career websites.

3. Online annoucements circulated on Walls and discussion forums of Facebook accounts associated with UNSW student clubs and societies on campus.

4. Email invitations sent to Heads of Schools, Heads of UNSW departments, Heads of residential colleges, and delegates of UNSW student clubs and societies for dissemination to staff and student mailing lists.

5. Paper posters and leaflets placed on billboards across the university campus.

